### Data collection and outcome measures

Unit Clinical Trials Nurses who recruit eligible patients will keep recruitment and clinic attendance logs. The dedicated funded Unit researchers will collect baseline clinical/demographic data either via a baseline clinic questionnaire, with demographic questions chosen as far as possible to match those included in the head and neck 5000 project [21], or by extraction from baseline clinical records. Baseline data will include cancer site, disease severity, HPV status, treatment details, gender, age, deprivation [IMD from post code], smoking, alcohol, and ACE-27 comorbidity. All clinical outcome data will be collected automatically via IPAD at each consultation. A data manager (based at Aintree) will have overall responsibility for ensuring data quality and integrity.

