#### Secondary outcome measures

Mean social-emotional subscale score of UW-QOLThe Aintree Research team was involved in developing the UW-QOL subscales, and the social-emotional subscale [20] is the mean of 6 domain scores (each 0–100) - anxiety, mood, pain, activity, recreation and shoulder function. The anticipated result in the control group is a mean score of 75.
2.Distress Thermometer (DT) score of 4 or more (range 0 to 10). The anticipated result in the control group is 34%. The Distress Thermometer (DT) is a single item self-report measure and has been used to screen for distress in various cancers [24–27]. A score of four and above denotes significant distress as this correlates with optimal sensitivity and specificity to the Hospital Anxiety Depression Scale [25, 28].

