### Sample size calculation

We have used nearly 20 years of accumulated experience with the UW-QOL to estimate a sample size that is pragmatic enough for a trial to be doable, yet able to detect meaningful differences if they exist. In regard to all UWQOL records collected the percentages of patients reporting less than good overall quality of life were relatively similar over different time periods from diagnosis and the expectation for the trial control group was taken as 30% after about 12 months. Cluster randomized trials require larger sample sizes than the individually randomised design because observations on individuals in the same cluster tend to be correlated, thereby reducing the effective sample size. The degree of correlation within consultant clusters, as estimated by the intra-class correlation (ICC) was estimated as barely above zero (6.7e-05) for consultants at Aintree. Assuming a likely control group outcome of 30%, an ICC value of 0.01 for the trial and not wishing to miss a halving in outcome rate, then a total of 312 patients from at least 10 consultants were required. After factoring a likely loss of 15% through patient mortality during the follow-up period and a possible maximum loss of 10% from initial non-consent, this then implied a total of 416 eligible patients needing to be approached for participation to the research. This number would also detect a moderate-sized clinical difference of 10 units (75 Vs. 85) in the mean composite social-emotional subscale score, for which an ICC estimate of 0.025 was obtained for consultants within Aintree. Data from an MD project with 325 HNC patients at Aintree gave an estimated 34% with a Distress Thermometer score ≥ 4, and the trial numbers would be sufficient to detect a halving in this outcome.

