### Statistical analysis

As inference will target the individual patient level, analyses will need to adjust for potential clustering in the data. We will report results for each group (PCI, non-PCI) and the estimated effect size from the use of PCI and its precision (95% confidence interval). For the primary outcome, we will report the intra-cluster correlation coefficient to assess the amount of clustering. In reporting results, we will follow the CONSORT statement extension applicable to cluster RCTs. We will use random effects (multi-level) logistic regression methods and will estimate the effect of PCI after making adjustment for relevant case-mix and for clustering effects of patients being within consultant clusters. Only baseline patient factors will be considered as case-mix adjusters and these include age, gender, treatment, overall clinical stage, tumour site and baseline clinic assessment of whether overall UWQOL was less than good (Y/N). A *P* value ≤0.05 is considered statistically significant. Secondary clinical outcomes will be analysed as per protocol.

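### The primary model adjusts for baseline overall QOL only as a Y/N indicator, leaving avoidable residual confounding in a trial where six of 14 consultants chose their arm

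*Protocol article*

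**What the plan says.** All references are to the protocol article.

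- **Model.** Under Statistical analysis: "We will use random effects (multi-level) logistic regression methods", with adjustment for case-mix and for clustering by consultant.
- **Adjusters.** The same section says: "Only baseline patient factors will be considered as case-mix adjusters and these include age, gender, treatment, overall clinical stage, tumour site", and adds "baseline clinic assessment of whether overall UWQOL was less than good (Y/N". The word Only limits adjusters to baseline patient factors. The list itself is introduced as an inclusive one. The form of the QOL term, however, is written out as binary.
- **Data held.** Under Study intervention, the questionnaires start at the first post-treatment clinic, which is the baseline. Controls complete the same measures apart from the PCI and its feedback form. Under Data collection and outcome measures: "All clinical outcome data will be collected automatically via IPAD at each consultation".
- **Allocation.** Under Method of randomisation, consultants with a strong preference were offered their preferred arm: three of six at Leeds (PCI) and three of eight at Liverpool (control). Leeds' other three had no preference and all went to control. One of Liverpool's remaining five was randomly allocated to control and four were left for PCI, giving seven consultants per arm.
- **Secondary outcomes.** "Secondary clinical outcomes will be analysed as per protocol". No model or covariates are given for them.

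**The concern.** Baseline overall QOL is the primary outcome's own baseline and plausibly its most important patient-level predictor. Cutting it at good treats all answers below the cut as equal, and all answers at or above it as equal. The outcome may stay binary; that does not require its baseline covariate to be binary.

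In a fully randomised trial this would be mainly a small loss of efficiency. Here six of 14 consultants chose their arm, so the patient mix may differ between arms for reasons other than chance, and the comparison leans on case-mix adjustment. A baseline difference within the two halves of the dichotomy passes into the estimated PCI effect.

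**Working it through.** **Inputs from the article:** control rate 30%, halving to 15%, ICC 0.01, 312 analysable patients from at least 10 consultants, 416 to approach (Sample size calculation); significance at 0.05; seven consultants per arm.

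**Assumed, because the article does not give them:** two-sided test, 80% power, six ordered answers, a normal latent QOL scale, baseline-to-one-year latent correlation 0.4 to 0.6, baseline shift between arms 0.1 to 0.3 SD.

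**1. The plan's own figure.** The premise is "Assuming a likely control group outcome of 30%, an ICC value of 0.01 for the trial and not wishing to miss a halving in outcome".

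- Per arm: [1.96·√(2·0.225·0.775) + 0.842·√(0.30·0.70 + 0.15·0.85)]² / 0.15² = 120.5, so 121 per arm and 242 in total.
- Design effect with 312/10 = 31.2 per cluster: 1 + 30.2·0.01 = 1.302.
- 242 × 1.302 = 315, within 1% of 312. Then 312/(1 − 0.25) = 416.

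The figures reproduce. They do not rely on covariate adjustment, so the present point does not alter them.

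**2. Information kept by the split.** For a normal covariate cut so that p = 0.30 lie on one side, the share of variance kept is φ(z)²/[p(1 − p)] = 0.3477²/0.21 = 0.576, a correlation of 0.76.

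**3. Residual confounding with no true effect.** These are simulated logistic models with the baseline shifted in favour of the PCI arm, so spurious odds ratios fall below 1. The share left is log(OR adjusted)/log(OR unadjusted).

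| Correlation | Shift (SD) | OR unadjusted | OR with Y/N | OR graded | Left by Y/N | Left by graded |
|---|---|---|---|---|---|---|
| 0.4 | 0.1 | 0.936 | 0.972 | 0.995 | 43% | 8% |
| 0.4 | 0.2 | 0.876 | 0.945 | 0.991 | 43% | 7% |
| 0.4 | 0.3 | 0.823 | 0.925 | 0.993 | 40% | 4% |
| 0.5 | 0.1 | 0.917 | 0.963 | 0.991 | 44% | 10% |
| 0.5 | 0.2 | 0.851 | 0.934 | 0.989 | 42% | 7% |
| 0.5 | 0.3 | 0.780 | 0.898 | 0.982 | 43% | 7% |
| 0.6 | 0.1 | 0.901 | 0.952 | 0.983 | 47% | 16% |
| 0.6 | 0.2 | 0.819 | 0.916 | 0.984 | 44% | 8% |
| 0.6 | 0.3 | 0.742 | 0.879 | 0.975 | 43% | 9% |

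A separate simulation with linear adjustment (correlation 0.4 to 0.6, shift 0.2 to 0.3 SD) left 45 to 47% with Y/N and 8 to 9% with six levels. Together the two give roughly 40 to 50% left by Y/N.

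**4. Power for 30% against 15%**, at effective N 312/1.302 ≈ 240:

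| Correlation | Unadjusted | Y/N | Graded | Gain over Y/N |
|---|---|---|---|---|
| 0.4 | 79.2% | 81.8% | 82.7% | 0.9 points |
| 0.5 | 80.1% | 83.9% | 85.3% | 1.4 points |
| 0.6 | 79.4% | 84.5% | 87.1% | 2.6 points |

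These models hold only arm and baseline QOL. The other named adjusters and the consultant random effect are left out.

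**The case against.** **The choice is coherent.** The Y/N term uses the primary outcome's own definition and cut-point, and matches the change in percentage used in the cost-effectiveness analysis. That stands: it is a defensible covariate, and it already removes more than half of the confounding. But nothing is gained by the coarsening.

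**The effect is small.** The target of 30% against 15% is an odds ratio of (0.15/0.85)/(0.30/0.70) = 0.41, beside which a spurious 0.88 to 0.97 is modest. The power gain is slight. Both stand. The bias would matter more if the true effect were smaller than a halving.

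**The imbalance is assumed.** In the simulation, shifts of 0.1 and 0.3 SD correspond to about 3 and 9 to 10 percentage points in baseline less-than-good QOL. At the planned ICC of 0.01, true consultant differences give a between-arm SD of √(0.01·0.21)·√(2/7) = 2.4 points, sampling error excluded, and the Aintree estimate of the ICC is lower still (6.7e-05). So the upper end of the range would need preference to be linked with patients' QOL, which the article does not show. This stands as a limit on size.

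**The repair may cost parameters.** With 156 per arm, expected events are 156·(0.30 + 0.15) ≈ 70, and several adjusters are already named. This counts against entering QOL as categories or adding further scores. It does not count against one linear term in place of one indicator.

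**Stronger readings that the document does not support.**

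- A reader might infer that the secondary outcomes' own baselines are ignored, since the social-emotional subscale "is the mean of 6 domain scores (each 0–100" and the 0 to 10 Distress Thermometer are also recorded at baseline. But the adjuster list follows a logistic model, which cannot be the model for a mean score, and the secondary analyses are deferred to the full protocol, which is not shown. Their baselines are unspecified here, not ignored. For the same reason, a loss of precision on all three clinical outcomes is not shown.
- A reader might infer that consultants largely chose the arms. Six of 14 did, and both arms are present at each site.
- The adjuster list is not closed, so nothing bars a further baseline score.

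**Conclusion.** The point holds for the primary outcome. Baseline overall QOL is fixed as a dichotomy although the graded answer is available in both arms, and under partly preference-based allocation this leaves residual confounding that could be avoided at no cost. Under the stated assumptions, Y/N adjustment leaves roughly 40 to 50% of the confounding carried by baseline QOL (spurious odds ratio about 0.88 to 0.97), against 0.98 to 1.00 with the graded answer. The precision argument is minor, at about 1 to 3 points of power.

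It is a worthwhile improvement to a stated choice, not a flaw that invalidates the primary analysis. Neither form of the covariate deals with confounding at consultant level: with seven consultants per arm and six self-selected, differences in how consultants practise remain.

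**What to change.** Prespecify, before outcomes are seen, that the primary model adjusts for the baseline overall-QOL answer as a linear ordered score in place of the Y/N indicator.

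The cost is one sentence. One parameter replaces another, the answers are already collected at the baseline clinic, and the 312 and 416 stay as they are. Fixing the form in advance matters, because a change of covariate after the results are known would be open to challenge. The report should still say that patient-level adjustment cannot remove consultant-level confounding.

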### Purpose of the study and hypotheses

The main purpose of this three-year research project is to investigate whether incorporating the PCI into routine head and neck cancer (HNC) follow-up consultations improves the overall QOL of patients. The Null hypothesis is that there is no difference between trial groups in the percentage of patients with less than good overall QOL at one year following the first baseline routine clinic post-treatment.

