### Method of randomisation

Problems of consultant contamination (from switching back and forth from using to not using the PCI package as would be required with conventional randomisation) indicate this should be a cluster RCT, in that consultants are randomised to ‘using or ‘not using’ the PCI at all their trial clinics. The steering group approved a randomisation process incorporating consultant preference; a method reported previously [19]. The aim is to limit the chance occurrence of PCI-sceptic consultants dominating the PCI group and PCI-enthusiastic consultants the non-PCI group. Those with a strong preference are offered their preferred group and those with no preference are randomised. The allocation process was overseen by the medical statistician involved, before any patient recruitment occurred. At Leeds, three of six consultants preferred to be in the PCI group, while the other three consultants had no preference as to group and were all allocated to the non-PCI control group. At Liverpool, three of eight consultants preferred to be in the non-PCI control group. One of the other five consultants was randomly allocated to the non-PCI control group, leaving four to be in the PCI group. Thus, at the two sites, seven consultants were in each arm of the trial.

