#### Primary outcome measure

The primary outcome measure is overall QOL, specifically the percentage with less than good overall QOL at the final one-year clinic as measured by the single UWQOL-v4 question [18]. The anticipated result in the control group is 30%. The UW-QOLv4 is a commonly used HNC specific HRQOL questionnaire [22, 23] and has been used with HNC patients at the Aintree Regional Head and Neck Unit since 1995. Over 1000 patients have completed over 5000 UW-QOL questionnaires giving the research team considerable experience in analysing and reporting this QOL measure.

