We will fully cost the delivery of the PCI intervention and associated costs such as training and other materials used. We will use published national average NHS reference consultant costs, accounting for overheads. From an NHS perspective, we will undertake a primary cost-effectiveness analysis of the PCI approach, using the change in % of patients with ‘less than good’ overall QOL between baseline and one-year as the outcome effect, and a subsequent cost-utility analysis using QALY as the outcome effect measured using the EQ-5D-5 L questionnaire. Costs of service use and QALY data will be derived from the CSRI and EQ-5D-5 L questionnaires collected at baseline, 3, 6, 9 and 12 months. The area under the curve method will be used to calculate QALYs, weighting survival by QOL weights obtained from the EQ-5D-5 L. We will compare our findings with unofficial NICE thresholds (ceilings) of £20,000 to £30,000 per QALY. Discounting is unnecessary given the time period. We will account for patient clustering, producing cost-effectiveness planes and acceptability curves (CEACs) to convey to policy makers the probability that PCI approach is cost-effective at different payer thresholds. We will undertake 5000 bootstrapped replications to generate confidence intervals around point estimates. The CSRI also allows us to account for the impact on healthcare service use from intervention participation, important when further rolling out the PCI approach.

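### The primary cost-effectiveness analysis takes change from baseline as its effect, not the baseline-adjusted one-year percentage that is the trial's primary effect

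*Protocol article*

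**What the plan says.** All references are to the protocol article.

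- **Clinical effect.** Primary outcome measure defines the outcome as overall QOL, "specifically the percentage with less than good overall QOL at the final one-year clinic". The null hypothesis (Purpose of the study and hypotheses) is of "no difference between trial groups in the percentage of patients with less than good overall QOL at one year".
- **Clinical model.** Under Statistical analysis, a multi-level logistic regression "will estimate the effect of PCI after making adjustment for relevant case-mix and for clustering effects of patients being within consultant clusters". The listed adjusters include "baseline clinic assessment of whether overall UWQOL was less than good (Y/N".
- **Economic effect.** The next paragraph of the same section sets the effect of the primary cost-effectiveness analysis as the change in the percentage with less than good "overall QOL between baseline and one-year as the outcome effect". On adjustment it says: "We will account for patient clustering, producing cost-effectiveness planes and acceptability curves (CEACs". It also plans 5000 bootstrap replications. It neither specifies nor excludes baseline or case-mix adjustment.
- **Allocation.** Method of randomisation: "Those with a strong preference are offered their preferred group and those with no preference are randomised". At Leeds, "three of six consultants preferred to be in the PCI group" and the three without a preference all went to control. At Liverpool three preferred control, and the other five were split by a random draw, one to control and four to PCI.

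**The concern.** The same baseline measurement is used in two ways. For the clinical effect it is a covariate; for the cost-effectiveness ratio it is subtracted. The two approaches estimate the same quantity only if the arms have the same baseline percentage or if baseline status fully predicts one-year status. Otherwise subtraction removes more of the baseline difference than carries over to one year, because of regression to the mean.

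At stake is the agreement between the two headline results. The incremental cost-effectiveness ratio (ICER) could suggest a gain that the clinical analysis does not show, or the reverse, purely through the handling of baseline. The change contrast is also the noisier of the two, so the cost-effectiveness plane and acceptability curves would be wider than the data require.

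A smaller point goes with it. Sample size calculation expects 15% mortality during follow-up. Unless the change is restricted to patients measured at both times, the baseline and one-year percentages describe different people.

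**Working it through.** **1. The plan's own figures.** Inputs from Sample size calculation: control 30%, halved to 15%, ICC 0.01, 312 patients, at least 10 consultants. With two-sided alpha 0.05 and 80% power (assumed; no power is stated), two proportions need 121 per arm, 242 in total. The design effect with 312/10 = 31.2 patients per consultant is 1 + 30.2 × 0.01 = 1.302, and 242 × 1.302 = 315, within 3% of 312. Then 312/(1 − 0.25) = 416. The sample size reproduces and is not affected by this point. The target effect is 30 − 15 = 15 points.

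**2. How far the two effects differ.** Let φ be the baseline-to-one-year correlation of the binary outcome (not in the documents). Assume a stable control percentage of 30%; the article says percentages were relatively similar over time. For a PCI arm with baseline percentage b and an additive effect d:

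- one-year percentage = 30 + φ(b − 30) + d
- baseline-adjusted difference = d
- difference in change = d − (1 − φ)(b − 30)

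The shift is (1 − φ) times the baseline imbalance: 0.7 points per point at φ = 0.3, 0.5 at φ = 0.5 and 0.3 at φ = 0.7.

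**3. Size of a chance imbalance.** With 312 patients under 14 consultants, the design effect is 1 + (312/14 − 1) × 0.01 = 1.213. Taking a 30% baseline, SE = √(2 × 0.30 × 0.70/156 × 1.213) = 0.057, or 5.7 points.

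**4. Effect on the ICER denominator.** The ratios hold the cost difference fixed and take a 15-point adjusted effect.

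| φ (assumed) | Shift for a 1-SE imbalance | Change contrast | ICER relative to adjusted |
|---|---|---|---|
| 0.3 | 0.7 × 5.7 = 4.0 | 11.0 or 19.0 | 15/11.0 = 1.36 or 15/19.0 = 0.79 |
| 0.5 | 0.5 × 5.7 = 2.9 | 12.1 or 17.9 | 15/12.1 = 1.24 or 15/17.9 = 0.84 |

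With no true effect and a purely illustrative 10-point imbalance, the change contrast alone shows 7, 5 or 3 points for φ = 0.3, 0.5 or 0.7.

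**5. Precision.** With equal percentages at both times, the change variance is proportional to 2(1 − φ) and the adjusted variance to 1 − φ². The ratio is 2/(1 + φ): 1.54, 1.33 and 1.18 for φ = 0.3, 0.5 and 0.7.

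**6. Steps 4 and 5 are one harm.** 2(1 − φ) − (1 − φ²) = (1 − φ)². Under chance imbalance, the extra variance is exactly the imbalance shift expressed as variance. The two must not be added.

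**The case against.** The strongest reply is that the wording names an outcome, not a model. In a linear model, regressing change on arm and baseline gives the same arm coefficient as regressing the one-year value on arm and baseline. If the economic analysis adjusts for baseline, the discrepancy disappears. Covariates for an economic model may sit in a plan not shown, and their absence from an article is no fault. This stands: the harm is conditional on a simple change contrast. It does not remove the stated mismatch between the economic effect and the primary outcome.

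A reader might infer more than the documents support:

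- **That the ICER will be biased.** If imbalance arises by chance, the change contrast is unbiased on average and the cost is precision, which a cluster-respecting bootstrap would show in its intervals. Where groups form by preference, neither method is guaranteed unbiased. If group differences are stable over time, change could be the unbiased contrast.
- **That the arms are non-randomised.** Six of 14 consultants were placed by preference, five were split by a random draw, and three at Leeds had no preference and were put in control without a described draw.
- **That baseline imbalance is likely.** Preference for a tool is not evidence of different patients. The Aintree ICC for this outcome was 6.7e-05, and the arms are balanced by centre (Leeds 3 and 3, Liverpool 4 and 4).

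The consequence is also bounded. The clinical test is unaffected, and the only decision threshold given, £20,000 to £30,000, is per QALY and belongs to the separate cost-utility analysis. The loss of patients between baseline and one year distorts the between-arm contrast only if losses differ by arm.

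**Conclusion.** The point holds as a stated choice that should be changed, not as a demonstrated bias. The primary economic effect differs from the trial's primary effect and, as a simple change contrast, is the less precise of the two. Its variance is 1.33 to 1.54 times the adjusted variance for φ of 0.5 to 0.3. Equivalently, a one-standard-error chance imbalance shifts it by 2.9 to 4.0 of the 15 points targeted.

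These sizes rest on an assumed φ, a 30% baseline, a stable control percentage, the planned 312 patients and ICC of 0.01, and no baseline adjustment in the economic model. At φ = 0.7 the excess variance falls to 18%. Preference-driven imbalance is not quantified, because the documents give no basis for it.

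**What to change.** In the economic paragraph of Statistical analysis, define the effect as the difference between arms in the percentage with less than good overall QOL at one year, adjusted for baseline status and the case-mix factors already listed for the clinical model, in the same patients as the primary analysis. Compute it together with costs in each bootstrap replicate, resampling in a way that respects consultant clusters. Keep change from baseline as a sensitivity analysis, restricted to patients with both measurements; this is worth having because covariate adjustment is not guaranteed unbiased under preference allocation.

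The cost is a short change of text and somewhat more analysis work, with no new data and no effect on the sample size. Refitting a multi-level logistic model 5000 times with 14 clusters may fail to converge in some replicates. A simpler baseline-adjusted model inside the bootstrap would avoid this and should be named in advance.

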## Methods/design

This is a preference cluster randomised control trial with consultants either ‘using or ‘not using’ the PCI at clinic. 416 HNC eligible patients from at least 10 consultant clusters are required to show a clinically meaningful difference in the primary outcome, that is having less than good overall QOL at the final one-year clinic as measured by the relevant question on the UWQOL-v4 [18].

Before treatment, eligible patients will be asked to consent to participation in the ‘research cohort’. Patients agree to their clinical data being used (Table 1) and to completing research questionnaires before each post-treatment consultation, some of which might be used in their consultation. Completion of all pre-consultation questionnaires including the PCI items will be by computer (desktop, tablet, IPAD). Quality Assurance is by initial training and later booster sessions for consultants and a post consultation survey of those in the PCI arm. Also, in the first six months of the study a random selection of clinic consultations will be taped in order to check how consultants do or do not use the PCI package.

**Table 1 Tab1:** Schedule for collecting clinical and demographic details

Timepoint		Trial Period	
	Enrolment	Baseline clinic	Follow up clinics
Gender	X		
DOB	X		
IMD 2015	X		
Smoking and Drinking Details		X	X^a^
Living Situation		X	
Employment		X	
Income		X	
Primary Diagnosis (ICD code)	X		
Tumour Site	X		
Treatment Plan	X		
Ethnicity	X		
TNM Stage	X		
Cancer Staging	X		
Histology (SNOMED)	X		
HPV Status	X		
Co-Morbidity	X		
ACE 27	X		

^a^Completion at patient 6 and 12 month study visit

A Steering Group is guiding the research and a joint-site Management group will manage it. Each site will have regular Project Team meetings to review progress. Day to day management issues will be addressed with each unit Lead Researcher. A data manager (based at Aintree R&D) will have overall responsibility for ensuring data quality and integrity. The study will last three years comprising of set-up and piloting, 12 months of recruitment, 15 months of follow-up and analysis, and then write-up and initial dissemination.

In analysis, the two patient groups will be compared after adjusting for relevant case-mix and for effects of patients being within consultant clusters. A summary flowchart of the key features of this trial is shown as Fig. 1.

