#### Cost-effectiveness

Quality-adjusted life year (QALY).Quality-adjusted life year (QALY) is used as a summary measure of health benefit for economic evaluation, using the EQ-5D-5 L health index to adjust for patient QOL [29, 30]. QALY is used as a common unit to allow comparisons across different interventions or disease areas [31]. EQ-5D-5 L is a validated generic, health-related, preference-based measure comprising mobility, self-care, usual activities, pain and discomfort, anxiety and depression. These are complemented by a visual analogue scale (VAS) [32], on which patients are asked to indicate their current health from 0 (worst imaginable health) to 100 (best imaginable health) [33].
2.Health service use and costsHealth service use by participating patients will be collected using a Client Service Receipt Inventory (CSRI). CSRI is a form that is usually administered in an interview setting or by self-completion via postal surveys or at clinics – asking them to recall retrospectively the type and frequency of their contacts with primary and secondary care NHS services. A CSRI form adapted to the study was developed using existing CSRIs, available from the DIRUM open access database http://www.dirum.org, as a reference and guidance with input from study researchers. For this trial, services such as physiotherapist, occupational therapist, social worker and others are included. To translate the service use into costs, unit costs from published sources will be applied to the patients’ self-reported service use data and the mean total cost of care per patient over 12 months will be calculated in each group. CSRI is the most common means of collecting service use data, usually with a short recall period of up to 6 months [34, 35], in health economics studies that require data across a range of health care settings. CSRIs were developed first in the field of mental health economics [36], and a review of their use is published by Ridyard and Hughes [37].
6.Cost of the PCI interventionResources and materials use for the delivery of the PCI intervention will be recorded and costed and the total cost of the PCI intervention will be calculated.

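### The QALY comparison names no adjustment for baseline EQ-5D-5L, so a baseline utility gap between partly preference-allocated arms would pass into the cost per QALY

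*Protocol article*

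**What the plan says.** The economic part of Statistical analysis sets out its steps in some detail. On QALYs: "The area under the curve method will be used to calculate QALYs, weighting survival by QOL weights obtained from the EQ-5D-5 L", from "questionnaires collected at baseline, 3, 6, 9 and 12 months". On uncertainty: "We will undertake 5000 bootstrapped replications to generate confidence intervals around point estimates". Results are to be judged against "unofficial NICE thresholds (ceilings) of £20,000 to £30,000 per QALY". The one correction named is for clustering: "We will account for patient clustering, producing cost-effectiveness planes and acceptability curves (CEACs". Under Cost-effectiveness, service use is priced with unit costs, and "the mean total cost of care per patient over 12 months will be calculated in each group".

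Two other places bear on adjustment. The opening of Methods/design says, without limiting it to any outcome: "In analysis, the two patient groups will be compared after adjusting for relevant case-mix and for effects of patients being within consultant clusters". The clinical part of Statistical analysis lists the case-mix factors, for a multilevel logistic model: age, gender, treatment, clinical stage, tumour site and a yes/no baseline version of the overall quality-of-life item. Baseline EQ-5D-5L is not on that list or named as a covariate anywhere else.

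On allocation, Method of randomisation says: "Those with a strong preference are offered their preferred group and those with no preference are randomised". It then gives the result for all 14 consultants.

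**The concern.** An area-under-the-curve QALY contains the baseline utility as its first point. If the arms differ at baseline, that difference enters the QALY difference directly. It also enters indirectly, because patients with higher utility at baseline tend to have higher utility later. Neither part is an effect of the intervention.

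The allocation makes this more than a formality. Some consultants took the arm they wanted, there are only seven per arm, and caseloads may differ between consultants. A gap in baseline utility would move the incremental QALY, and with it the cost per QALY, the plane and the probability of cost-effectiveness at each threshold. The listed case-mix factors would capture such a gap only in part. The one baseline health-status measure among them is a yes/no item from a different instrument, which is a coarse stand-in for a utility index.

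**Working it through.** **Plan figures.** The article states no EQ-5D mean, SD, QALY or cost, so no economic figure can be reproduced. The 312 patients used below can be: 30% against 15%, two-sided 5% and an assumed 80% power (power is not stated) need 121 per arm. The design effect is 1 + (312/10 − 1) × 0.01 = 1.302, and 2 × 121 × 1.302 = 315, close to 312. Then 312/(1 − 0.15 − 0.10) = 416, as stated.

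**Allocation (Method of randomisation).**

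| Site | PCI arm | Control arm |
|---|---|---|
| Leeds (6) | 3 by preference | 3 without preference, all placed in control, no draw described |
| Liverpool (8) | 4 left after the random draw | 3 by preference, 1 by random draw |

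By preference: 3 + 3 = 6 of 14 (43%). In a described random draw: 4 + 1 = 5 of 14 (36%). The remaining 3 of 14 had no preference and no described draw.

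**Weight of the baseline value.** With measurements at 0, 3, 6, 9 and 12 months, the trapezoid weights are 0.125, 0.25, 0.25, 0.25 and 0.125. For a baseline gap d and a slope b of later values on baseline, the shift in the QALY difference without baseline adjustment is

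d × (0.125 + 0.875 × b).

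**Size (d and b are assumptions; the thresholds are the article's).**

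| d | b | QALY shift | at £20,000 | at £30,000 |
|---|---|---|---|---|
| 0.03 | 0.4 | 0.03 × 0.475 = 0.014 | £285 | £428 |
| 0.03 | 0.6 | 0.03 × 0.650 = 0.020 | £390 | £585 |
| 0.05 | 0.4 | 0.05 × 0.475 = 0.024 | £475 | £713 |
| 0.05 | 0.6 | 0.05 × 0.650 = 0.033 | £650 | £975 |

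The limits are 0.125d if the gap exists only at baseline and 1.0d if it persists in full.

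**Is such a gap plausible?** Under full randomisation of 14 consultants, the standard error of the baseline difference is SD × √(2/156 × [1 + (312/14 − 1) × ICC]). With an assumed SD of 0.20 to 0.25 and an ICC of 0.01 to 0.025, this is 0.025 to 0.035. A gap of 0.03 is then 0.9 to 1.2 standard errors, and 0.05 is 1.4 to 2.0. This is chance alone; any selection through preference comes on top.

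**Effect on a decision (all inputs assumed).** Take a true gain of 0.02 QALY and an extra cost of £250, so £250/0.02 = £12,500 per QALY. A 0.03 gap with b = 0.5 shifts the QALY difference by 0.03 × 0.5625 = 0.0169. The ratio becomes £250/0.0369 = £6,780 if the gap favours PCI and £250/0.0031 = £80,000 if it favours control (unrounded denominators 0.036875 and 0.003125).

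**The case against.** The strongest reply is that the article does not say costs and QALYs will be compared unadjusted. A reader might infer a comparison of raw group means corrected only for clustering, but that would be drawn from silence. The general statement in Methods/design promises case-mix adjustment and does not exclude the economics. The sentence on mean cost per group describes a summary, not the estimator of the arm difference. A condensed article may also leave regression covariates to a fuller plan. All of this stands. It removes any claim that the plan fixes an unadjusted analysis, and with it the inference that an adjusted clinical result is bound to sit beside an unadjusted economic one.

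A reader might also describe the arms as largely self-selected. The count does not support that: 6 of 14 consultants took a preferred arm, and the three Leeds consultants placed in control had no preference. Consultants are balanced by site, 3 against 3 and 4 against 4. Preference is described in terms of attitude to the PCI, and nothing in the article shows that patient mix differs by consultant.

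The sizes are assumed. A gap of 0.05 lies towards the tail of chance. Expected mortality of 15% weakens the carry-forward, since utility after death is zero whatever the baseline. If the listed case-mix factors are applied to QALYs, they would absorb part of the gap.

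What the reply does not reach is baseline utility itself. Even if the general statement covers the economics, its listed factors leave out the one variable that is a component of the QALY.

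**Conclusion.** The point holds in a limited form. The economic part of Statistical analysis specifies area-under-the-curve QALYs and names clustering as its only correction. The general promise of case-mix adjustment may extend to costs and QALYs, but neither it nor the covariate list includes baseline EQ-5D-5L. In a 14-consultant trial with only 5 consultants in a described random draw, a baseline utility gap would pass at least in part into the incremental QALY and everything built on it.

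The illustrative size is 0.014 to 0.033 QALY, or £285 to £650 per patient at £20,000 per QALY. This rests on an assumed gap of 0.03 to 0.05, assumed slopes of 0.4 to 0.6 and no other covariate absorbing the gap. It shows sensitivity and does not demonstrate a bias. The point concerns the cost-utility analysis and the wording on cost adjustment. It does not concern the effect measure of the primary cost-effectiveness analysis, which is already a change from baseline. It is a worthwhile improvement to the stated method, not a fatal flaw.

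**What to change.** In the economic part of Statistical analysis:

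- State that the case-mix adjustment promised in Methods/design, with the factors listed for the clinical model, also applies to 12-month costs and QALYs.
- Add the baseline EQ-5D-5L index as a covariate in the QALY model, and keep a consultant effect in both models.
- Build the 5000 bootstrap replicates, the cost-effectiveness plane and the acceptability curve from these adjusted differences.
- Report unadjusted means by arm as description.

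The cost is wording and a little more analysis. By the Study intervention section, EQ-5D-5L is completed while waiting for each consultation from the baseline clinic onwards, so the baseline value precedes the first trial consultation. The case-mix factors are already collected. No baseline cost is needed, so the change does not depend on the CSRI schedule. That schedule does need reconciling: Study intervention gives 6 and 12 months, while Statistical analysis gives baseline, 3, 6, 9 and 12 months. Adjustment removes the measured baseline gap in expectation; it does not remove unmeasured differences between consultants who chose their arm.
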